## Methods

### Study design

This study is a superiority randomized controlled trial with multiple arms: two experimental groups and one care-as-usual-only as the control group. Based on equivalence, the two intervention groups receive care-as-usual plus a mentoring intervention called Mentor Support. The difference between these two groups is determined by the VI of the mentors and not by the way Mentor Support is performed. One group receives Mentor Support from a mentor with a visual impairment and one group from a sighted mentor. The effectiveness of this randomized controlled trial will be tested with pre-test, post-test, and follow-up. This study protocol has been approved by the Ethics Committee of the VU University (VCW.1310.010; Netherlands Trial Register NTR4768).

### Study population

Adolescents (*N* = 120) aged between 15 and 22 years with VI are the target population. This study defines visual impairment as “impairment in vision, which even with correction affects an adolescent’s social participation” and, thus, includes both blindness and partial sight. No up-to-date population count of adolescents with VI in the Netherlands exists. Past research estimated the number to be around 1,000 people for an age range of 14 to 25 years [5]. For the seven-year age range used in this study (15 to 22) this could be estimated at 500. The minimum response rate is therefore 24 % if the total population can be reached.

Inclusion criteria are: diagnosed with a visual impairment, age between 15 and 22 years, and living in the Netherlands. Exclusion criteria are: having severe additional impairments, such as complete deafness or intellectual disabilities, and not mastering the Dutch language. For the 120 mentees, 40 mentors will be recruited, half of them having a visual impairment. During Mentor Support mentors will accompany a maximum of two mentees.

### Intervention

Mentor Support is a mentoring intervention developed for adolescents with VI. The primary purpose of Mentor Support is to improve social participation of these adolescents in three domains: 1) work/school, 2) leisure activities, and 3) social relations [9].

In total, Mentor Support consists of 12 face-to-face meetings of the mentee with a mentor within an overall time period of one year. On a weekly basis, dyads also have contact via email, the Internet, or telephone. The joint meetings take place in or near the mentee’s own (usually home) environment and are mostly executed “outside”. Every domain of social participation consists of four meetings, which can be performed in diverse order. Activities accomplished during the meetings are based on mentees’ ambitions and self-designed goals. During Mentor Support mentees gather information, possible actions, and strategies, through modeling, to improve their social participation.

Positive thinking and having success experiences are the main focus of these meetings. Examples of activities can be visiting an (unknown) sports club, gallery, or restaurant, inviting and making friends, and visiting the workplace of the mentor (see Table 1). Mentors and mentees will keep record of their experiences and reflect on their meeting through an evaluation form. All meetings are accompanied by a specially designed systematic handbook consisting of assignments, exercises, and example activities. These tools can also be downloaded by the mentors and the mentees from the Mentor Support website, which is especially designed and accessible for persons with VI. Mentors and mentees have to upload their completed evaluation forms, assignments, and exercises, and, therefore, the website is also used to coordinate the intervention. Modifying the intervention and creating an individualistic path or personalized course is prohibited for several reasons, such as health-related problems within the direct family or moving to another part of the country during Mentor Support.

**Table 1 Tab1:** Description of themes and domains of each Mentor Support meeting

	Themes of activities	Domain of social participation
Meeting 1	Basic conversation skills first meeting	Social relationships
Meeting 2	Sports and searching for possibilities	Leisure activities
Meeting 3	Timeframe development for the future	School/work
Meeting 4	Life space mapping	Social relationships
Meeting 5	Job visit and searching for vacancies	School/work
Meeting 6	Hobbies and searching for possibilities	Leisure activities
Meeting 7	Preparing a party and inviting new friends	Social relationships
Meeting 8	Presentation skills and appearance	School/work
Meeting 9	Out of the box or out of your comfort zone	Leisure activities
Meeting 10	Searching for your motto in life and role model(s)	School/work
Meeting 11	Discussing romantic relationships, flirting and dating	Social relationships
Meeting 12	Evaluating the intervention during special leisure activity	Leisure activities

Participants randomized to the control group will receive only care-as-usual. The two national organizations for people with VI in the Netherlands offer a wide range of services, such as mobility training, and itinerant teacher support at school. At pre-test, post-test, and follow-up all participants are asked about the kind and amount of care-as-usual service they have received.

### Procedure

#### Mentees

Participants will be recruited through two national service organizations (Bartiméus and Royal Dutch Visio) for people with VI. These organizations have multiple rehabilitation centers, have special education schools all over the Netherlands, and also offer itinerant teacher support to adolescents with VI in regular education. These organizations will send a recruitment brochure and cover letter to inform all clients/students who meet the inclusion criteria and their parents. Clients/students who do not participate will remain anonymous to the researcher. Participants are also to be recruited through online banners, brochures on social media, Internet/magazine/website advertisements, and brochures distributed by several associations for people with VI.

If participants decide to participate, they sign up for this study, with their name and email address, via the website. After signing up, the participants are asked questions about demographic factors, their visual impairment, and possible additional impairments. If participants meet the inclusion and exclusion criteria for this study, they and their parents (if the participant is under 18) receive an official information letter and informed consent form. After signing and sending back the informed consent, they are then eligible to participate in this study. Because signing and sending back the signed informed consent could be challenging for people with VI, participants are allowed to sign the consent form by placing a cross (X) in a box and sending it back by email. Printing and signing by hand is therefore not needed. This procedure has been established with the approval of the Ethics Committee of the VU University.

Once the informed consent is sent back to the researchers, participants receive a baseline measurement (T1). Data will be collected in the Netherlands in their own home environment through computer-assisted telephone interviews. These interviews are conducted by several trained researcher assistants using online survey software called Qualtrics. An interview lasts about one hour and 30 minutes and contains several questionnaires. After this baseline measurement, every participant is randomly allocated to one of the experimental groups or the care-as-usual-only group. The results from the randomization will be sent to the participants in the experimental group (mentees) by email, and the care-as-usual-only group will be informed by telephone.

#### Mentors

All voluntary mentors of Mentor Support will be extensively selected and trained before starting. First of all, the mentors have to sign up through the website, where they enter background information, such as age, impairments, and educational/working achievements. Based on this, eligible mentors will be invited for an intake by telephone. This structured interview contains questions about their own social participation, life experience, and prospects of mentoring. Next, expectations about the intervention will be discussed in order to distinguish eligible mentors. After the intake phase, mentors are invited to attend the Mentor Support mentoring training. Before attending, mentors receive an information letter and have to sign an informed consent. The Mentor Support mentoring training is developed and held at VU University and is partly based on knowledge and experiences from other mentoring programs in and outside the Netherlands. It consists of topics such as: the background and design of the intervention, information about having VI, do’s and don’ts related to etiquette with VI people and safety, information about trust and privacy, and establishing a positive mentor-mentee relationship. During this eight-hour training, mentors have to practice their newly acquired skill by role playing and through assignments about problem scenarios which could occur during the Mentor Support intervention. The training is guided by a train-the-trainer manual. After successfully completing the training, mentors must submit a certificate of good conduct. This document, which must be requested from their own city office, declares that the mentor did not commit any criminal offences that are relevant to the performance of their duties. With this last step, mentors are eligible to accompany mentees. The main objective for mentors, executing the Mentor Support intervention, will be to share life experiences, in order to support their mentee(s). Research has shown that mentors benefit from participating in mentoring programs [29]. Possible positive outcomes could be, for example, an improvement in their social skills, meeting new people, and possibly developing new friendships. After finishing Mentor Support, all mentors receive an official certificate.

#### Matching

Matching the mentees and mentors is first based on their geographic proximity and subsequently on their similar interests. These interests are measured with a questionnaire. After all mentors and mentees are matched, the primary researcher will notify them by email, and within the same month these dyads begin with the Mentor Support intervention. Directly after Mentor Support has ended, a post-test and a follow-up, after six months, measurement among all participants will be conducted. Figure 1 illustrates the different steps and stages of the research procedure. During the study participants receive information about the study progress through a newsletter. All participants receive a summary report about the effects of Mentor Support at the end of the study.

**Fig. 1 Fig1:**
[figure not shown]
Research procedure

### Randomization

Upon signing the informed consent, before randomization, participants agree to be allocated to one of the three groups. An independent researcher will randomly assign participants at an individual level to one of the three arms of this randomized controlled study. The allocation will take place with a computerized random number generator after the baseline measurement and before the start of the intervention. Randomization stratification on the important factor of geographic proximity will be used to make sure there is equal allocation to regions. Blocking randomization in each region with a block size of 15 participants will be used to strive for regional groups with the same size. The independent researcher will keep the results of the randomization until the study is completed and all eligible participants are allocated. During the study the primary researcher and participants are not blinded. Only the researchers measuring the post-test and follow-up will be unaware of who is allocated to which arm.

### Measures

#### Primary outcome measures

The main question of this study is whether adolescents with VI improve their social participation after participating in Mentor Support. Several questionnaires will be used to measure social participation within the three domains: work/school, leisure activities, and social relationships.

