##### Work/education

To measure type of education, history of education (special or regular schools), and level of education, three closed-ended questions will be used. For employment, 11 questions measuring type of job, voluntary or unpaid employment hours, travel hours, side jobs, and the maximum working hours per week are asked.

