##### Social relationships

The Social Network Map [5, 6, 38–40] will be used to measure the size and composition of the social network of the adolescents. With this scale each sector or category such as family, extended family (for example, uncle, aunt, niece), friends, and professionals/therapists can be outlined. It measures the amount of people in each sector and the importance of these relationships. Social support will be measured by the personal network list (PNL) with the role-relation method [3, 41]. This seven-item questionnaire measures the social support during leisure activities, problems at school/work, and social relationship problems with answers ranging from 10 “not important” to 100 “really important”. The internal consistency was found to be .76, .79, and .81 [41]. Satisfaction with the social network is measured with two items: “*How satisfied are you with the support you get with practical problems?”* and *“How satisfied are you with the support you get for personal problems?”.* Answers are given on a five-point scale. Developing and maintaining romantic relationships is a common interest during adolescence [14, 42, 43]. To assess this topic, 12 questions will be used, for example, “*Do you have a romantic partner*?”, “*How long has this relationship lasted*?”, and “*Have you ever fallen in love?*”.

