### Sample size

The total sample size is based on the expected differences in outcome measures between participants assigned to the experimental arm receiving Mentor Support and the care-as-usual-only arm. For testing the significance of the between-subject factor (primary hypothesis) a sample of 120 participants (40 in each condition) is necessary to achieve an adequate power of .85 within a medium effect size (d = .5) between the conditions over time with a significance level of .05. Due to dropout or unexpected organizational aspects the number of participants could drop to as low as 108 to achieve a high power of .80. To answer the research question concerning the influence of potential mediators or predictors on the effectiveness of Mentor Support, several repeated measures within-between interaction analyses will be performed. Based on a significant level of .05 and a power of .85 (*f* = .25), a total sample size of 110 is needed.

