### Data analyses

Most analyses will be conducted using the software program Statistical Package for the Social Sciences (SPSS). The descriptive analyses will be carried out using standard methods. If necessary, outliers will be checked and winsorized before analyzing. Differences in baseline characteristics between both experimental groups and the care-as-usual-only group will be analyzed and results will be controlled for these differences if needed. For analyzing the primary (social participation on three domains), mediation (psychosocial functioning and self-determination), and predictor (demographic factors and personality) outcomes, ANOVA repeated measures or multilevel analyses will be used. The primary outcomes of participants in both experimental groups will be compared separately from the care-as-usual-only group. Pre-test, post-test, and follow-up will show the change in quantity and quality of social participation, psychosocial functioning, and self-determination as compared with the care-as-usual-only group, over time. Feasibility of the Mentor Support intervention will be analyzed using descriptive analyses. General mixture modeling with M-plus [58] will be used to examine the impact of the Mentor Support intervention on subgroups. Analyses and reporting of the results will be done according to the CONSORT Statement guidelines.

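### No primary outcome or time point is fixed: about 12 instruments count as primary, each mentor arm is compared with control, and the sample size covers one test at .05

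*Protocol article*

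**What the plan says.** Under Primary outcome measures, the protocol article states: "Several questionnaires will be used to measure social participation within the three domains: work/school, leisure activities, and social relationships". Four subsections sit below that heading:

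- **Social participation:** the adapted VAP, with two subdomains.
- **Work/education:** "To measure type of education, history of education (special or regular schools), and level of education, three closed-ended questions will be used", plus 11 employment questions.
- **Leisure activities:** the peer activity list, 20 leisure questions, four Internet questions, an adapted social media scale and an online support scale.
- **Social relationships:** the Social Network Map, the personal network list, two satisfaction items and a block on romantic relationships ("To assess this topic, 12 questions will be used").

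Mediators, predictors and control variables have headings of their own, so these measures are set apart as the primary ones.

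Data analyses adds: "The primary outcomes of participants in both experimental groups will be compared separately from the care-as-usual-only group". Sample size states that "a sample of 120 participants (40 in each condition) is necessary to achieve an adequate power of .85", assuming "a medium effect size (d = .5) between the conditions over time with a significance level of .05". No other significance level is given for the primary hypothesis. The main hypothesis under Hypotheses is directional and speaks of Mentor Support as a whole against care-as-usual.

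**The concern.** The article does not say which result would confirm or refute the main hypothesis. Many scores, two arm comparisons and two later time points are available, and any of them could be presented as improved social participation. The planned size allows for one test. Participants and the primary researcher are not blinded and the outcomes are self-reported by interview, so an outcome chosen after the data are seen would be hard to defend.

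Some listed measures also cannot carry the hypothesis. History of education can barely respond to a year of mentoring, and passive social media use has no stated direction of improvement.

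**Working it through.** **1. The plan's own figure.** From Sample size: N = 120, d = .5 (f = d/2 = .25), α = .05, power .85. From the design: 3 groups and 3 measurements. The correlation between repeated measurements is not stated; I assume ρ = .5. For the between-groups test in a repeated-measures ANOVA:

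λ = f² · N · m / (1 + (m − 1)ρ), with 2 and N − 3 degrees of freedom.

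- N = 120: λ = .0625 × 120 × 3 / 2 = 11.25, critical F = 3.07, power .851.
- N = 108: λ = .0625 × 108 × 3 / 2 = 10.125, critical F = 3.08, power .809.

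In steps of 3, the smallest N is 120 for .85 and 108 for .80. Both stated sizes are therefore recovered by one three-group test on one outcome.

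**2. Counting what is primary.**

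- Instruments or question blocks: VAP, education, employment, peer activity, leisure questions, Internet use, social media scale, online support, Social Network Map, personal network list, network satisfaction, romantic relationships = 12.
- Scale scores: VAP 2, peer activity 1, social media 3, online support 1, network size and importance 2, personal network list 3, satisfaction 2 = 14. Treating the satisfaction items as one score gives 13.
- Single items: 3 + 11 + 20 + 4 + 12 = 50.

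The count of 14 assumes that the adapted social media scale keeps the three dimensions of the original and that the three reliabilities reported for the personal network list mean three scores. I use 12 to 14 as the range.

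**3. Chance of at least one false positive.** Suppose each score is tested at two-sided .05 in both arm comparisons. Null trials were simulated with equal arms A and B and a shared control C: z₁ = (A − C)/√2 and z₂ = (B − C)/√2, with a common correlation r between outcomes. The documents give no r, so it runs from 0 to .7. A positive is |z| > 1.96; a favourable positive is z > 1.96.

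| Scores × 2 comparisons | Counted | r = 0 | r = .3 | r = .5 | r = .7 |
|---|---|---|---|---|---|
| 3 (one per domain) | either direction | 25% | 24% | 22% | 19% |
| 3 | favouring Mentor Support | 13% | 12% | 11% | 10% |
| 12 | either direction | 68% | 61% | 51% | 38% |
| 12 | favouring Mentor Support | 43% | 33% | 26% | 19% |
| 14 | either direction | 74% | 66% | 55% | 41% |
| 14 | favouring Mentor Support | 48% | 36% | 28% | 21% |

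A single two-sided test gives 5% in either direction and 2.5% in the favourable one.

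**4. Pooled arms.** With one comparison of both mentor arms together against control, 14 scores give 51, 44, 35 and 25% in either direction at r = 0, .3, .5 and .7, and 30 to 12% in the favourable direction. Pooling lowers the figures but does not bring them near the nominal level.

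**5. One outcome, two comparisons.** A single primary score tested in both comparisons with a shared control still gives about 9% two-sided. Naming one outcome is therefore not enough if the arms stay separate.

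The single items are not in these figures. Testing them, or testing post-test and follow-up separately, would raise the figures.

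**The case against.** A reader might infer that every questionnaire is tested at .05 and that a chance confirmation of the main hypothesis is more likely than not. The documents do not support either statement. The .05 stands only in Sample size; the article does not say that it applies to each score, or that any one success suffices. The main hypothesis is directional, so a result favouring care-as-usual does not confirm it. Counting only favourable results, the figure for 12 to 14 scores stays below 50% at every correlation tried. Even in either direction, it falls to about 40% at r = .7.

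A reader might also infer that categorical items cannot be analysed as planned. But Data analyses offers multilevel analyses as an alternative to repeated-measures ANOVA, and such models can handle binary and count outcomes.

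Finally, this is a condensed article. Scoring rules and a multiplicity adjustment may stand in an analysis plan that is not shown, and the abstract frames the outcome as social participation in three domains rather than as dozens of items.

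These points limit the size of the claim, but its core stands. The choice of primary outcome belongs in the protocol because it determines what the sample size covers. The article does not leave that choice out: it states a primary set and fixes it too broadly. A later correction would also need power that Sample size does not provide. On the narrowest reading, three domain scores in the two stated comparisons, the two-sided error is still 19 to 25%.

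**Conclusion.** The concern holds in this form: the article names no key measure, composite or primary time point among about 12 primary instruments, plans two arm comparisons, and supports its size with one test at .05. If each score is tested at that level, the chance of at least one false positive is about 19 to 25% with one score per domain and 38 to 74% with 12 to 14 scores. In the direction of the hypothesis it is about 10 to 13% and 19 to 48%, against 2.5% for one test.

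These ranges rest on an assumed correlation of 0 to .7, equal arms, the score count above, and no adjustment. They show what the text leaves open and do not predict how the trial will be analysed.

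**What to change.** Before outcome data are analysed, choose one of two routes and write it into the protocol.

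1. **One primary outcome at one time point**, for example a VAP participation score at the 12-month post-test. Test it either with the mentor arms pooled against care-as-usual, which matches the main hypothesis, or for each arm with Holm across the two comparisons. The choice should not rest on the reliability of .91, which was reported for the original ten-domain questionnaire; this trial uses an adapted version with five domains.
2. **One named score per domain at one time point**, with Holm across all 3 × 2 = 6 domain-by-arm tests. The first step is then at .05/6 = .0083.

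In both cases, make the remaining scales secondary and the single items descriptive, and restate the power for the chosen test or tests.

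**Cost.** Some measures lose primary status, and the power may look less favourable. At d = .5, two-sided .05 and a single measurement, power is about 73% for 80 against 40 and 61% for 40 against 40, or 50% for the latter at .025. Using the repeated measurements could change these figures. Recruitment and data collection were still in progress when the article was written, and the article says that changes in study procedures go first to the Ethics Committee, so the change needs a submission there.
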